#### Study part 2: retrospective cohort study

Data of patients who switch health insurance or decease within their individual observation period will be censored from claims data.

The claims database with be analyzed with descriptive statistics, more precisely summary statistics (measures of central tendency, spread, and dispersion), and frequency distributions. We use stratified analyses and multivariate modelling (logistic regression and generalized linear models) to estimate the influence of potential risk factors. The data structure requires multi-level regression models for cluster effects: On a patient level, we estimate the influence of case-mix variables (e.g., age, sex, comorbidity, nursing care level) on each specified outcome within a potential CD quality indicator (see section “Study outcomes”). On a facility level, we estimate the influence of quality of acute hospital care on each specified outcome within a potential CD quality indicator.

The existence of further cluster effects at IRF level will be explored. CD quality indicators will only be adjusted for risk factors an IRF has no control over, e.g., a patient’s age. Relevant measures to assess goodness-of-fit for logistic regression models are Hosmer-Lemeshow-test, Receiver Operating Characteristic (ROC Curve), Area under the curve (ROC AUC) and pseudo-R2 [50]. For general linear models, a robust estimator for estimation of covariance matrix is used.

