#### Study 2: retrospective cohort study

Included in the study 2 sample will be all AOK-insured patients that underwent primary hip or knee arthroplasty due to osteoarthritis and participated in orthopedic inpatient follow-up rehabilitation between 2018 and 2023. Cases are identified in the SHI claims database using the diagnoses and procedures described in Table 1, based on the respective yearly version of the International Classification of Diseases 10, German Modification [29] and the German Operation and Procedure Codes (OPS, [30]).

**Table 1 Tab1:** Inclusion codes for retrospective cohort study

Procedures and diagnoses	Codes
Hip joint replacement	OPS: 5-820.0, 5-820.8, 5-820.9, 5-820.x
with discharge diagnoses	ICD-10: M05-M08, M16, M87
Knee joint replacement	OPS: 5-822.0, 5-822.g, 5-822.h, 5-822.j, 5-822.k
with discharge diagnoses	ICD-10: M05-M08, M17, M87

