#### Study 2: retrospective cohort study

Based on data from previous years, we expect around 27,000 patients nationwide participating in follow-up rehabilitation after knee joint replacement and 25,000 patients participating in follow-up rehabilitation after hip joint replacement, amounting to a study population of around 52,000 patients per year. Since study 2 includes patients from 2018 to 2023, the total study sample will be around 312,000 patients.

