#### Study 2: retrospective cohort study

Since study 2 is exploratory in nature, no CD outcomes have yet been identified. The following steps will be taken for selection and operationalization of CD outcome variables, CD quality indicators, and CD risk factors:

A structured search for existing quality indicators, outcome variables, and risk factors of orthopedic rehabilitation will be conducted in (a) literature (e.g., Medline, Cochrane Library), (b) medical guidelines (Guidelines International Network), (c) indicator databases (e.g., [42, 43], and (d) documentation of existing procedures of quality assurance in the field of orthopedic rehabilitation. Search results will be assessed for their compatibility with claims data.The nationwide project claims database of AOK-insured patients will be analyzed to identify additional complex healthcare and rehabilitation outcomes for patients that have undergone primary knee or hip arthroplasty. This includes analysis of demographics, medical and other relevant data such as comorbidities, nursing care level, medication use, and utilization of therapeutic health service. The database will encompass data from the individual observational period for each patient, which includes the 24 months pre-surgery as well as 12 months of care after orthopedic rehabilitation. Pre-surgery data will be used as a baseline measure of study population characteristics, while the follow-up period after rehabilitation can be used to identify individual changes in relation to the baseline.Results from step (1) and (2) will be consolidated and CD outcomes and risk factors operationalized. Potential CD outcomes that represent aspects of rehabilitation treatment quality within claims data could be, for example, mobility (through provision of mobility aids), pain medication, or progression to higher nursing care levels. CD outcomes will consider care and quality aspects from all medical sectors. All quality indicators will be defined by denominators and numerators, and descriptions of inclusion, exclusion and exception criteria [44]. Denominators display a specified target population (e.g., all patients undergoing arthroplasty), whereas numerators display the number of people in the target population experiencing a specified outcome (e.g., surgical complications; [44]). These descriptive definitions can later be used to calculate individual values for rehabilitation facilities. Indicators will be translated into coded data (e.g., coded diagnoses, procedures, and prescriptions), and an appropriate reference value will be defined for each indicator.Each CD quality indicator will be adjusted for risk factors that have statistical influence on the indicator rate but cannot be influenced by IRFs. Risk factors might include patient characteristics (e.g., age, sex, comorbidity, nursing care level), or aspects of acute hospital care before rehabilitation. Relevant risk factors will be selected based on current research, results from SHI data analyses, and expert opinion [45].

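### The only calibration measure named for the Study 2 logistic models is the Hosmer-Lemeshow test, whose p-value at about 312,000 patients does not show whether misfit is large enough to matter

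*Protocol article*

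**What the plan says.** The data analysis section for Study 2 plans "multivariate modelling (logistic regression and generalized linear models) to estimate the influence of potential risk factors", with multi-level models for cluster effects. On the fit of the logistic models it states: "Relevant measures to assess goodness-of-fit for logistic regression models are Hosmer-Lemeshow-test". The full list of measures is "Hosmer-Lemeshow-test, Receiver Operating Characteristic (ROC Curve), Area under the curve (ROC AUC) and pseudo-R2". No alpha, threshold or accept/reject rule is attached to any of them.

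The purpose of the models is given under Study outcomes for Study 2: "Each CD quality indicator will be adjusted for risk factors that have statistical influence on the indicator rate". Under Practical implications, the facilities are to receive individual report cards built on key quality indicators.

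The sample size section for Study 2 says: "Since study 2 includes patients from 2018 to 2023, the total study sample will be around 312,000 patients".

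**The concern.** A risk-adjusted indicator compares a facility's observed rate with the rate expected for its patients. If expected risk is wrong for, say, older patients or those with a higher nursing care level, facilities that treat more of them are misjudged. Calibration, and above all the size of any miscalibration, is therefore the property that matters.

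The ROC curve and AUC describe discrimination, and pseudo-R2 describes explained variation. That leaves the Hosmer-Lemeshow test, whose statistic grows in proportion to the number of patients for a fixed misfit. In a sample this large, a small p-value can come from a negligible error or a serious one, and the p-value does not tell them apart. The standard test also treats patients as independent, while the same section says the data are clustered.

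**Working it through.** **Inputs from the article.** 27,000 knee and 25,000 hip patients a year, "amounting to a study population of around 52,000 patients per year", who "participated in orthopedic inpatient follow-up rehabilitation between 2018 and 2023", i.e. six years.

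**The article's own figure.** (27,000 + 25,000) × 6 = 312,000, which reproduces exactly. By joint: 27,000 × 6 = 162,000 knee and 25,000 × 6 = 150,000 hip.

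**Assumptions not in the article.** Ten risk groups, 8 degrees of freedom, alpha 0.05 (critical value 15.51), and event rates p of 5%, 10% and 20%. The claims-data outcomes are not yet identified, so a range is shown.

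**Formula.** If predicted risk is off by d in every risk decile, and every decile is given the same event rate p for simplicity, the statistic is approximately noncentral chi-square with noncentrality n·d²/[p(1−p)]. The rejection probability is the chance that it exceeds 15.51.

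**Example.** n = 312,000, p = 0.10, d = 0.0025: 312,000 × 0.00000625 / 0.09 = 21.7, which gives 93.8%. With d = 0.005 the noncentrality is 86.7, which gives about 100%.

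| Patients | Error d | p = 5% | p = 10% | p = 20% |
|---|---|---|---|---|
| 312,000 | 0.25 points | 99.9% | 94% | 69% |
| 162,000 (knee) | 0.25 points | 93% | 65% | 38% |
| 150,000 (hip) | 0.25 points | 91% | 61% | 35% |
| 312,000 | 0.5 points | ~100% | ~100% | ~100% |
| 162,000 (knee) | 0.5 points | ~100% | >99.9% | 97% |
| 150,000 (hip) | 0.5 points | ~100% | 99.9% | 96% |

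For contrast, with n = 3,000 and p = 10% the same 0.5-point error is rejected in only 8%.

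**Check with a more realistic misfit.** Here decile risks vary (standard deviation of the linear predictor 0.8, overall event rate 10%) and a small quadratic term of 0.05 is left out. The mean decile gap is 0.34 points and the largest is 0.86. The calculated rejection rate is 7% at n = 3,000, 67% at 52,000, 99.5% at 150,000 and about 100% at 312,000. Simulation (100 runs per size) gave 11%, 64% and 100% at 3,000, 52,000 and 312,000. A correctly specified model was rejected in 5.3% of 150 runs at 312,000, so the test holds its level with independent patients. The problem is its sensitivity to small errors.

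**Can the other listed measures fill the gap?** In every omitted-term scenario, the AUC of the misfitting model and of the true model agreed to four decimals (0.7173 in the example above). AUC does not register this misfit.

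**Would calibration intercept and slope help?** Not in the fitting data. The score equations of an ordinary maximum-likelihood logistic fit make the residuals sum to zero and be uncorrelated with the linear predictor. Refitting the outcome on that predictor therefore returns intercept 0 and slope 1. Two simulated misfitting models at 312,000 gave exactly 0 and 1, while the Hosmer-Lemeshow statistic was 42 in one and about 93 in the other.

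**The case against.** The case on the other side has several parts.

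- **No decision hangs on the test.** The article lists it among relevant measures without a rule. H1 and H2 are tested by other means, and risk factors are chosen from research, claims analyses and expert opinion. This stands. A reader might infer that good models will be judged to fit poorly, but the article does not say how a significant result would be used.
- **A non-significant result would be reassuring.** At this sample size it would point to close calibration, and the observed and expected counts behind the test show the size of the misfit. This also stands. A reader might infer that the test cannot show anything about adequacy, which goes too far. It is the significant p-value that says nothing about size.
- **Over-sensitivity is not uniform.** Single-joint models are plausible, since the joints are defined by separate codes and stratified analyses are planned. For 0.25-point errors they are rejected in only 35% to 38% at a 20% event rate. The ranges above include this.
- **An article need not spell out calibration plots or subgroups.** True, and their absence alone is no finding. The point here is the choice the article does make: the one calibration measure it names suits the stated sample size poorly.
- **Clustering.** The plan already calls for multi-level models, and the effect of clustering on the test has not been quantified. The conclusion does not rest on it.

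**Conclusion.** The concern holds in limited form. As the sole calibration measure named for logistic models on about 312,000 patients, the Hosmer-Lemeshow p-value does not separate relevant from irrelevant misfit. Half-point decile errors are almost always rejected (96% to 100%). Quarter-point errors are rejected in 69% to 99.9% pooled and 35% to 93% for one joint. These figures rest on the assumed event rates, alpha 0.05, ten groups and, in the table, a uniform error across deciles. The check with varying decile risks points the same way.

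The consequence is confined to how the fit of the indicator risk models is judged. No hypothesis test is affected. The change is still worth making because those models feed facility comparisons and the repair is nearly free.

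**What to change.** In the Study 2 analysis section:

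- Report the Hosmer-Lemeshow p-value as descriptive only, with no role in accepting or rejecting a model.
- Judge calibration by size: a smoothed calibration plot, observed versus expected rates by risk decile, and the mean absolute calibration error. Give these overall and by joint, age group and nursing care level.
- Report calibration intercept and slope, with confidence intervals clustered by facility, only in held-out data such as a random split or later calendar years.
- Keep AUC and pseudo-R2 for discrimination and explained variation.

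The cost is a change of wording and slight extra analysis. Held-out assessment also needs a validation split, which a sample of this size can afford. No new data are needed.

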## Discussion

Health claims data has the potential to simplify current quality assessments in rehabilitation. SEQUAR will evaluate its benefit to quality assurance in orthopedic inpatient rehabilitation: We will explore outcome variables and quality indicators based on readily available statutory health insurance (SHI) claims data, and assess their ability to replace select parts of the current best-practice quality assurance protocol based on arduous primary data collection. If we fail to identify suitable claims data quality indicators, we can demonstrate that the current protocol of assessing patient-reported and physician-reported outcomes via questionnaires is still to be considered the best-practice approach. In the process, we are hoping to improve risk-adjustment models used to evaluate inpatient rehabilitation facility (IRF) quality by incorporating cross-sectoral SHI quality data (i.e., quality of the operating hospital) that could help adjust for risks outside of an IRF’s control.

Many previous studies have explored the utility of claims data in quality of care research. Some have even taken a cross-sectoral approach, like Stegbauer et al. [51] or Bramesfeld et al. [52], though the latter had to cut their trial phase short because–fittingly–the burden of primary data collection for participating physicians proved to be too great. However, to our knowledge, no study has examined claims data’s cross-sectoral potential for quality assurance in inpatient rehabilitation (where quality assessment is particularly difficult due to the variety in outcomes), nor has any research explored the possibility of replacing patient- and physician-reported outcomes with outcomes based on claims data.

If successful, further research is required to examine whether our findings are applicable to other indications of rehabilitation. SEQUAR focuses on a sample of post-op arthroplasty patients, since the underlying disease (gonarthrosis/coxarthrosis) and its degenerative effect is localized to a specific joint, diagnosed with an objective set of criteria, and treated with a limited number of specific surgical interventions [53–56]. Arthrosis primarily affects objective areas of functioning (such as walking, using stairs, doing yard work), and its subsequent rehabilitation program has an unambiguous primary outcome goal: to restore (painless) mobility [55, 56]. Objective impairment–as opposed to impairment that can only be measured via introspection, like symptoms of depression–can most likely be more easily described using (mostly objective) claims data. Other rehabilitation indications differ in their therapeutic programs and have other superordinate goals: Neurological rehabilitation after stroke seeks to restore motor function and strengthen adaptive strategies [57]; oncological rehabilitation focuses on coping and other psychosocial outcomes [58]; and cardiovascular rehabilitation targets lifestyle risk factors (e.g., nutrition, smoking, and lack of movement; [59]). If we identify an indicator that can reliably represent a more generic outcome of rehabilitation (e.g., restoring or improving strength, endurance, or flexibility), it should transfer to other indications. The more introspective and (strictly speaking) non-medical the outcome (e.g., nutrition, or psychosocial aspects), the harder it will be to approximate with health claims data.

### Practical implications

The ultimate goal of SEQUAR is a novel, state-of-the-art quality assurance protocol for orthopedic rehabilitation that incorporates identified claims data quality indicators and reduces the amount of patient- and physician-reported primary data required. The protocol will be developed in collaboration with nursing and medical staff from participating IRFs. IRFs will receive individual report cards with key quality indicators based on our results to identify and remedy internal quality management issues.

### Strengths

SEQUAR’s design of linking claims data-determined outcomes with primary data-determined outcomes (using the current best-practice protocol) allows for evaluation of proximity of the two on an individual patient level. The claims database in SEQUAR is very large, nationwide, and cross-sectoral—and reusing readily available, existing data not only in our research, but also in quality assessments nationwide, could result in significant reduction of required resources (e.g., paper questionnaires, servers to store primary datasets, financial burden on IRFs).

### Limitations

While the claims database used in SEQUAR is large, it is sourced from only 11 (of the over 90 existing) statutory health insurers in Germany, whose members make up only about 37% of SHI insured Germans. The identification process of claims data outcomes will not be universal, as each SHI has a distinct structure to their claims databases.

Primary data collection also comes with a known set of challenges: Longitudinal studies frequently struggle with dropout at follow-up, particularly 6 months after the fact [31–33]. Since IRFs and patients volunteer their participation, there will be some self-selection bias in our sample. Additionally, regional AOK representatives pre-selected IRFs that were known to be cooperative and interested in quality management research, which results in further selection bias. Participants that decease during the study period are censored from data analysis, leading to a potential underestimation of negative outcomes and inappropriate fit of our models for those patients with worse health at baseline.

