**Fig. 1 Fig1:**
[figure not shown]
Data flow in SEQUAR

We will use the matched dataset to test our hypotheses:

For H1a, CD outcome variables should be able to serve as surrogates (proxies) for rehabilitation treatment outcomes as measured by current best-practice assessment (PD outcome variables; see outcome assessment and study design in high-quality studies on the effectiveness of multidisciplinary orthopedic rehabilitation—e.g., [28]). For H1b, we assume at least a moderate correlation (> 0.30) between CD quality indicators and PD quality indicators. To test H2, the impact of cross-sectoral CD risk factors (on patient and facility levels) on current risk-adjustment models for quality assessment will be investigated.

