### Study population and recruitment

#### Study 1: prospective longitudinal study

For study 1, ten German inpatient rehabilitation facilities (IRFs) were enlisted in the study by local representatives of the regional AOK health insurance funds, which in turn are recruiting a planned sample of 600 patients. Participating IRFs signed a collaboration agreement with the principal investigator, and each appointed a local study coordinator in charge of organization and implementation of all project tasks (e.g., recruitment of participants, distribution of patient information and consent forms, storing/safekeeping signed consent forms). Patient recruitment began in November of 2022 and will end in December 2023.

Patients eligible for participation are recruited on-site in the beginning of their orthopedic follow-up rehabilitation. Study coordinators present them with a physical copy of the study fact sheet (covering study synopsis, data protection, and other legal aspects), and ask for their participation. Those agreeing to participate sign an informed consent form. Eligibility is determined by meeting the inclusion criteria: Participants must be at least 18 years old at time of inclusion (beginning of rehabilitation), insured through AOK health insurance fund (for purposes of data availability), and receive inpatient orthopedic follow-up rehabilitation after implantation of a knee joint replacement or hip joint replacement due to osteoarthritis. Participants need to demonstrate sufficient knowledge of the German language and sufficient cognitive abilities to answer the comprehensive questionnaires independently. Patients that prematurely discontinue rehabilitation, demonstrate insufficient German or cognitive skills, or change health insurance within the study period will be excluded.

Participation in the study is incentivized with a €50 gift voucher for patients that complete all four questionnaires, while IRFs receive €120 per patient for full patient participation and completed case report forms.

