### Sample size

#### Study 1: prospective longitudinal study

Recruiting IRFs are encouraged to assess every patient for eligibility (as per the inclusion criteria), with a target sample of 60 participants per facility totaling *N* = 600 cases. Assuming an initial refusal quota of 30% (non-response), IRFs need to approach 860 patients, or 86 patients per facility. Withdrawal of consent or loss to follow-up throughout the data collection phase are estimated to result in an average dropout rate of 20% for each time point, which will reduce the initial target sample by approximately 50%. Thus, we expect a sample of n = 300 to remain for analysis (comparable studies report dropout rates of 25–55%, depending on the length of observational period; [31–33]). Figure 2 visualizes the sample flow in a CONSORT flow diagram.

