#### Study part 2: retrospective cohort study

Claims data is sourced from the health claims databases of all 11 regional AOK health insurance funds. A project database will be compiled to include claims data from inpatient/hospital and outpatient care, medication, remedies and aids, as well as information on nursing care level and demographics. Additional data on the quality of the operating hospital is available through the established quality assurance procedure QSR [11]. The individual observation period for each patient includes 24 months before initial hospital admission and 12 months after follow-up rehabilitation. Figure 3 illustrates what data will be included in the project database and their statutory source in the German Social Code (see also section “Quality Assurance in German Rehabilitation”).

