If at least two of the three validation criteria are met, the tested CD outcome variable is considered an adequate proxy for the respective PD outcome variable. Bland-Altman plots will be used for graphic evaluation of measurement differences [47, 48]. This same procedure will be applied to test H1b using CD quality indicators and PD quality indicators, which are represented by facility group mean values of PD outcome variables.

##### Hypothesis 2

H2 postulates an improvement in risk-adjustment models when considering cross-sectoral claims data, i.e., an increase in (adjusted) R^2^, and will be analyzed with nested multilevel regression models. A basic model (M0) will be estimated for each PD outcome variable using the PD confounders (see Table 2) on level 1. Models will be estimated for each time point after baseline (t1, t2, t3), and will be adjusted for *time* (rehabilitation effect) as a predictor on level 2. Furthermore, level 2 PD quality indicators will be included. Each model will be expanded with previously identified CD risk factors (on level 1 and level 2) as described in section “Study outcomes”. The nested models will be compared with Likelihood Ratio tests [49]. The analysis sample will be randomly divided into two parts, with one half allocated for analysis of risk-adjustment, and the remaining half used to validate the resulting models.

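### H1b rests on ten IRFs chosen for their interest in quality management; their spread against all IRFs is not reported, yet the Discussion draws an unrestricted conclusion from a failure

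*Protocol article*

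**What the plan says.** Study population and recruitment (Study 1) states that "ten German inpatient rehabilitation facilities (IRFs) were enlisted in the study by local representatives of the regional AOK health insurance funds". The Limitations add how they were chosen: "regional AOK representatives pre-selected IRFs that were known to be cooperative and interested in quality management research, which results in further selection bias". The article calls this selection bias but draws no consequence for any hypothesis.

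H1b concerns facility-level agreement between claims data (CD) and primary data (PD) quality indicators, and the article describes its criterion in two ways. Study design and methods, below Figure 1, says: "For H1b, we assume at least a moderate correlation (> 0.30) between CD quality indicators and PD quality indicators". The end of the Hypothesis 1 analysis section says: "This same procedure will be applied to test H1b using CD quality indicators and PD quality indicators". That procedure has three criteria (accuracy, reproducibility, precision), of which two must be met.

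The Discussion states that, if suitable claims indicators are not found, "we can demonstrate that the current protocol of assessing patient-reported and physician-reported outcomes via questionnaires is still to be considered the best-practice approach". The sentence is not limited to the kind of facility studied.

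For the claims side, the Data collection section says: "Claims data is sourced from the health claims databases of all 11 regional AOK health insurance funds". Study 2 includes all AOK-insured patients with the relevant surgery and inpatient rehabilitation from 2018 to 2023, about 312,000. The Study 2 outcomes section says that the indicator definitions can yield values for individual facilities. No comparison of the ten IRFs with the others is mentioned.

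**The concern.** In H1b the facility is the unit of analysis, and a correlation between facilities depends on how far they differ. IRFs picked because they engage with quality management may be more alike than IRFs in general. If so, 0.30 is a harder target in this group than across all IRFs, and a low value could say more about who was enlisted than about the indicator. The other criteria also depend on the spread, but not in the same direction.

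At stake is how far the H1b result reaches. SEQUAR aims at a quality assurance protocol for orthopedic rehabilitation in general. A reader of the results could not tell whether the ten IRFs cover the usual range of quality, although the claims data that would show this, on the claims side, are already in the project database.

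**Working it through.** **The plan's own figures.** No power or precision figure is given for H1b. The Study 1 sample flow reproduces:
- Target: 10 × 60 = 600.
- To approach at 30% refusal: 600 / 0.70 = 857, stated as 860 (10 × 86).
- After 20% dropout at each of three later time points: 600 × 0.8³ = 307, stated as 300.

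H1b therefore has ten units, with about 30 analysed patients each.

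**Correlation criterion.** Let R be the CD-PD correlation across all IRFs and u the SD ratio defined as the between-IRF SD of the CD indicator in the ten IRFs over that in all IRFs. If selection acts through the CD indicator and the relation is linear with constant residual variance, the correlation in the ten is

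r = R·u / √(1 − R² + R²·u²).

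The article does not give u, so it is an assumption. For R = 0.50 and u = 0.5: 0.25 / √(0.75 + 0.0625) = 0.28.

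| u (assumed) | r in the ten if R = 0.40 | r in the ten if R = 0.50 | R needed for r = 0.30 |
|---|---|---|---|
| 1.0 | 0.40 | 0.50 | 0.30 |
| 0.9 | 0.37 | 0.46 | 0.33 |
| 0.8 | 0.33 | 0.42 | 0.37 |
| 0.7 | 0.29 | 0.38 | 0.41 |
| 0.6 | 0.25 | 0.33 | 0.46 |
| 0.5 | 0.21 | 0.28 | 0.53 |

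The last column is the inverse, R = (r/u) / √(1 − r² + r²/u²) at r = 0.30. If the ten IRFs were more varied than the rest, the effect would reverse: at u = 1.2, 0.50 becomes 0.60 / √(0.75 + 0.36) = 0.57.

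Simulating ten IRFs under bivariate normality with R = 0.50, the chance that the sample correlation exceeds 0.30 is 0.77 at u = 1, 0.62 at u = 0.7 and 0.49 at u = 0.5.

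**Slope and SD criteria.** Accuracy requires the slope interval (b ± 2 SE) to include 1 and the intercept interval to include 0. Precision requires the CD SD not to exceed the PD SD. A narrower CD range leaves the slope unbiased but widens its interval, and it shrinks the CD SD more than the PD SD. Simulation with ten IRFs, assuming R = 0.50, equal SDs across all IRFs and selection on the CD indicator:

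| u (assumed) | Slope interval includes 1 | CD SD ≤ PD SD |
|---|---|---|
| 1.0 | 58% | 50% |
| 0.7 | 74% | 82% |
| 0.5 | 83% | 96% |

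The same narrowing thus lowers the chance of passing the correlation level and raises the chance of passing these two checks.

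**Sampling error with ten units.** Fisher's z with SE 1/√7 gives a 95% CI around r = 0.30 of -0.41 to 0.78. Two-sided significance at 5% needs |r| of at least 0.63. With a true correlation of zero, the sample value exceeds 0.30 in 20% of samples.

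**How well u can be estimated.** The 95% CI of an SD on 9 degrees of freedom runs from 0.69 to 1.83 times the estimate. An observed u of 0.7 is compatible with 0.48 to 1.28. Correcting an observed r of 0.30 with u = 0.7 gives 0.41, with a span of 0.24 to 0.55 from the uncertainty in u alone.

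**The case against.** The strongest reply has four parts.

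1. *The premise is not documented.* Selection was on cooperation and interest, not on measured quality. No section gives a spread or says that poorly performing IRFs are absent. This stands: narrowing is an assumption, and u = 1 or above cannot be excluded. It is a reason to measure u, not to ignore it.
2. *The direction is not fixed.* A reader might infer that the selection pushes H1b towards failure, so that an indicator which works nationwide would be rejected. The article does not support that, because H1b is also tested by the Hypothesis 1 procedure, where a narrower claims spread can favour acceptance.
3. *The database cannot repair the correlation.* A reader might infer that claims for all IRFs allow a standard range correction (Thorndike case 2). That correction assumes direct selection on the CD indicator, whereas selection was on a third characteristic. There are no questionnaire data outside the ten IRFs. An SD ratio freed of sampling noise would be applied to a correlation of noisy means from about 30 patients per IRF. Set against 0.30, the corrected value would also raise false acceptance when the true correlation is zero, from 20% to about 27% at u = 0.7 and 33% at u = 0.5. This stands.
4. *The bias is disclosed, and the Discussion sentence concerns the whole search for indicators, not H1b alone.* This is true in part. But the disclosure does not limit the conclusion, and H1b is the facility-level part of that search. A failure in ten selected IRFs does not demonstrate that questionnaires remain best practice.

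It is also fair that the imprecision from ten units exceeds the possible selection effect.

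**Conclusion.** The point holds in a limited form. The ten IRFs were selected on a characteristic that may be related to quality, the H1b result depends on their spread, and the Discussion sets no limit on what a failure would mean. If u is 0.5 to 0.8, a correlation of 0.50 across all IRFs falls to 0.28 to 0.42 in the ten, and 0.53 to 0.37 across all IRFs is needed to show 0.30. These sizes rest on an assumed u, on selection acting through the CD indicator, and on a linear relation with constant residual variance. At u = 1 there is no loss.

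The documents do not establish that the range is narrower, that H1b is biased towards failure, or that the effect can be corrected. What they do support is that the position of the ten IRFs should be reported and the conclusion confined to the range they cover.

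**What to change.** - Calculate each CD quality indicator for all IRFs in the AOK project database. Report the mean, percentiles and between-IRF SD of the ten IRFs against all IRFs, taking the SD from a multilevel model so that patient-level sampling noise is removed, with a confidence interval for the SD ratio.
- Reword the Discussion so that an H1b result, negative or positive, applies only to the quality range the ten IRFs cover, and so that a failure is not called a demonstration that questionnaires remain best practice.
- Reconcile the two descriptions of the H1b criterion (the 0.30 level and the two-of-three procedure), since spread acts on them in different directions.
- Treat a range-corrected correlation as at most an optional exploratory figure, shown with its interval and assumptions and not set against 0.30.

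The cost is extra tabulation in data already held and a more modest conclusion. The change does not cure the imprecision from ten IRFs, which should be stated beside the result.
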